### Confidentiality

For all participants, we will take strong measures to protect confidentiality. Our privacy standards match those of the countries that we are recruiting in. For US participants, we have obtained an NIH Certificate of Confidentiality. All study personnel will be required to complete comprehensive training in confidentiality and privacy. When interviewing participants, we will offer meetings by secure, HIPAA-protected zoom calls; participants have the option to turn off their camera during those meetings.

Once a participant is enrolled in the study, a study ID will be assigned, and this ID will be used in place of identifying personal information such as a name on all assessment materials. The list linking the IDs and names will be destroyed after study completion. All data will be encrypted and kept on a password-protected computers that can be accessed only by study personnel. Consent forms, payment information and contact information will be filed separately from the research records. Data for this project will be gathering REDCap, a highly secure and robust web-based research data collection and management system. Features of REDCap that protect participants' privacy and data security include data storage on servers located in ITG's Advanced Computing Center providing locked physical security; use of both an OHSU firewall and a second ACC firewall; data transmissions that are encrypted with industry-standard SSL methods.

## Intervention content

We will be careful to inform participants that our study does not involve dieting and that we expect them to sustain their caloric intake throughout the intervention. Both interventions will be administered as self-help via online and app-based instruction supplemented with optional coaching sessions. The format, timing, and intensity of online and app-based coaching for the two interventions will be entirely parallel.

To minimize attrition and nonadherence, the intervention is limited to 8 weeks. Participants are welcome to continue to follow the food plan after the assigned 8 weeks and they will retain access to intervention materials. Consistent with multiple guidelines, all intervention content was reviewed by individuals with personal and family experience with BD to integrate their suggestions about the utility and refinement of the material [109, 110].

During the baseline period, we will use principles of motivational interviewing to ask participants about their own personal reasons for making changes in their food plan. We will also provide psychoeducation about “SMART” goals, including making one small change in habits at a time and avoiding self-criticism about days in which it is difficult to follow the plan. Participants will receive supportive reminders and praise for completing key components of the daily monitoring entries.

When participants are informed of their assigned intervention condition, they will receive a several-page resource guide with detailed instructions, tips, and advice for how to follow that plan (see intervention description below). Participants will receive more detail on the benefits and how to address potential barriers to the plan through brief blogs (generally one page or less) 2–3 times per week throughout the 8-week intervention period. Much of the educational content has been developed and used in previous trials of TRE and the Mediterranean Diet, but we will provide some tailored content for BD. Resource guides and blogs will be made publicly available at the end of the trial.

Because interactive support improves adherence to web interventions [111], both interventions include personal coaching support through asynchronous email contact with a trained coach, as well as opportunities to schedule a 15-min online videoconference or phone session. Participants will be given opportunities to email or to schedule 15-min sessions for coaching about barriers they face with implementing the food plan. We will encourage an initial coaching session when participants learn about their randomization and a second coaching session one week into the intervention period. At one, three, five, and seven weeks into the intervention, they will receive a link offering them a chance to email us or to schedule appointments for coaching if they would like (by clicking on a link to a calendar and specifying phone or video conference). Participants will be instructed that the scope of this coaching is narrow and will only focus on the dietary intervention. Participants can send as many messages as they like to their coach and will receive one response per week. Coaching sessions will also be limited to no more than one a week. Participants will be invited to bring significant others, family members or household members to the coaching sessions if they like.

Coaches will receive a set of guidelines and will meet with licensed clinical psychologists regularly throughout the intervention for support and to ensure that coaching maintains fidelity to the scope planned. Coaches will aim to provide a supportive, nonjudgmental environment where participants can discuss barriers and difficulties in implementing dietary plans and can receive behavioral tips. The focus of coaching will be on collaborative problem solving and empowerment in addressing barriers. Coaches will aim to help participants lessen self-criticism and to be sensitive to mood fluctuations that may make following this type of program difficult. Coaches will aim to help participants identify material in blogs, video clips, or other barriers materials that might help address the concerns raised.

Participants will also have access to a website of information designed to address barriers to following their food plan (e.g., coping with food cravings, adapting the Mediterranean Diet to culturally preferred foods), improving sleep, or addressing light exposure. Barriers were identified by reviewing previous studies using TRE or the Mediterranean diet, by conducting a survey of individuals with BD who had tried TRE, and by reviewing concerns raised by those with lived experience of BD and/or following dietary programs. For each major barrier, brief tips are available, which vary in format (written, audio, or video); all tips are designed to take 2 min or less. To help participants access relevant materials, they will be sent a quick survey at the end of weeks 3, 5, 7, and 9 in the program asking if they had experienced any of the core barriers and providing the option to view relevant tips.

### Time-Restricted eating

TRE involves restricting the window of eating to 10 h per day. To make that happen, people typically avoid eating in the first 1–2 h after they wake up and in the 2–4 h before they go to sleep. Participants will log the timing of their food intake during the baseline weeks. At the time of randomization, they will receive a graph of that data, along with a guided worksheet to help set the eating window that works best for them.

Those with an eating window greater than 14 h will be asked to restrict their eating to 12 h in the first week and then 10 h in the second week. When selecting the eating window, we will ask them to consider family meals and social commitments and will review logs from baseline to help identify those social engagements. We will also review past week sleep schedules, to plan for avoiding food 2–3 h before sleep. In setting the start time for eating in the morning, we will review any special energy demands, such as exercise, and the time periods that might work for eating given family and work commitments. Participants will be reminded not to restrict their caloric intake. As one example, people who habitually snack at night will be coached to consider ways to add calories to their regular mealtimes to avoid hunger. We will also proactively review potential barriers, such as family attitudes toward meal schedules and children’s meal timing. We also will plan ahead for upcoming holidays and vacations that may disrupt following the plan.

During the fasting period, only water, unsweetened herbal tea or black coffee, and prescription medication are permitted. During the feeding window, no restrictions are placed on the type or quantity of food consumed. We will instruct participants to follow their habitual diet within the specified consistent 10-h period and to aim to consume the same number of calories per day as they did during the baseline.

Blogs and orientation materials will provide support for keeping eating within the time window, including ways to share the food plan and goals with family and friends, ways to have easily prepared foods on-hand to avoid delays in eating dinner, and suggestions for portable breakfast ideas that would allow one to eat during a mid-morning break at work. During the third and fourth weeks of the TRE intervention, participants will receive two blogs to provide brief educational content on sleep and circadian rhythms and then two blogs to provide tips for improving sleep and circadian rhythms.

To monitor the timing of eating, participants will be asked to log each time they consume food or beverages (except water) using a cellphone app. Participant logs will be reviewed at least twice per week, and participants will be sent feedback if they appear to not log, to struggle with the time window, or to restrict the time window or caloric intake beyond the recommended goals.

### Mediterranean diet

The Mediterranean Diet is a plan for healthy eating based on how people eat and drink in the 16 countries that border the Mediterranean Sea. Individuals will be encouraged to consume vegetables (6 servings/day), fruits (2–4 servings/day), whole grains (daily), legumes (3–4 times per week), nuts (0.5 oz per day), and oily fish (2 servings/week). Participants will be encouraged to choose lean meats and other sources of protein over red meat and processed meats. Sweets (including desserts and refined cereals), alcohol, and wine or alcohol will be labeled extras, and participants will be encouraged to limit their consumption of extras. The Mediterranean diet resource kit provided at the time of randomization will include a list of key foods, a plan for setting feasible goals for change in the first week, an outline for planning grocery shopping, suggestions for following the Mediterranean diet on a budget, healthy snack options, and tips for finding recipes that meet cultural or food allergy guidelines. Interventions will be followed for eight weeks. To match the burden and self-monitoring of the TRE condition, participants in the Mediterranean diet condition will also be asked to log their food intake using the app.

## Measures

The schedule of the assessments is provided in Fig. 1 and Table 2. Assessments are performed as closely as possible to specified time points. Interviews will be conducted by HIPAA-compliant zoom or, if the participant prefers, by telephone. Participants will be sent calendar links to sign up for their interview assessments. Self-report assessments will be completed online via a secure, encrypted online survey platform (REDCap). Logs and EMA will be conducted using cellphone apps. Self-report measures and logs will be reviewed for completion and signs of carelessness, and follow-up will be conducted as warranted.

**Fig. 1 Fig1:**
[figure not shown]
Assessment Timing

**Table 2 Tab2:** Schedule of assessments

Measure	Format	Screening	Baseline	Mid-Intervention	Post-Intervention	Week 17 Follow Up	6, 9, 15 Month Follow Ups
***Screening Self-Report***							
DIAMOND Self Report Screener, Psychosis Subscale	SR	X					
Alcohol Use Disorders Identification Test (AUDIT)	SR	X					
Drug Use Disorders Identification Test (DUDIT)	SR	X					
Short Eating Disorder Examination Questionnaire (EDE-QS)	SR	X		X	X		
Insomnia Severity Index (ISI)	SR	X					
Munich ChronoType Questionnaire (MCTQ)	SR	X	X	X	X		X
Brief Social Rhythms Scale (BSRS)	SR	X	X	X	X		X
***Screening Interview***							
Orientation, Memory and Concentration Test (OMC)	I	X					
Diagnostic Interview for Anxiety, Mood, and OCD and Related Neuropsychiatric Disorders (DIAMOND)	I	X					
Columbia Suicide Severity Rating Scale (C-SSRS)	I	X					
Structured Clinical Interview for Sleep Disorders—Revised (SCISD-R)	I	X					
***Mood Assessments***							
Montgomery-Asberg Depression Rating Scale (MADRS)	I		X	X	X		X
Young Mania Rating Scale (YMRS)	I		X	X	X		X
Longitudinal Interval Follow-up Evaluation (LIFE)	I			X	X		X
Patient Mania Questionnaire (PMQ-9)			X	X	X	X	X
Patient Health Questionnaire (PHQ-9)			X	X	X	X	X
Patient Global Impression (PGI)	SR			X	X	X	X
Clinician Global Impression (CGI)	I			X	X		X
***EMA of Emotion States***							
Mood Zoom (MZ)	App		8 days	8 days			
***Quality of Life***							
Brief Quality of Life in Bipolar Disorder (QoL.BD)	SR		X	X	X		X
***Secondary Outcome Measures***							
Rey Auditory Verbal Learning Test	I		X		X		
WHO Disability Assessment Schedule 2.0-Brief	SR		X		X		
General Anxiety Disorder-7 (GAD-7)	SR		X		X		
Rapid Measurement Toolkit-20 (RMT20)	SR		X		X		
Godin Shephard Leisure-Time Physical Activity Index	SR		X		X		
***Intervention Acceptability Probes***							
Ratings of the acceptability of the Intervention	SR				X		
***Treatment Adherence***							
Food Logging	App		Daily	Daily			10 days- first & last intake
Food Frequency Questionnaire (FFQ)	SR		2 days	2 days			
Sleep Household Environment and In-Bed Behaviors	SR		X		X		
***Potential Mechanisms of Change***							
Core Consensus Sleep Diary (CORE CSD)	App		10 days	10 days			
PROMIS: Sleep Disturbance and Sleep-Related Impairment Scales	SR		X	X	X		X
***Potential Moderators***							
Personality Inventory for *DSM-5*, Brief Form Plus” (PID5BF +)	SR		X				
Positive Urgency Scale	SR		X		X		
Household Food Security Survey (HFSSM)	SR		X				
Menopause QoL items on sleep disruption (for women ages 45–65 (MENQoL)	SR		X				
Risky Families	SR		X				
Somatotherapy	SR	X	X	X	X	X	X
Demographics	SR		X				
Credibility and Expectancy Questionnaire – Credibility Set	SR		X				

Note.* App* Application, *I* Interview, *SR* Self-report

### Screening questionnaires

DIAMOND Self Report Screener [78]. We will administer the DIAMOND Self Report Screener psychosis subscale, a well-validated index of psychotic symptoms.

Alcohol Use Disorder Identification Test (AUDIT; [69, 79, 112]**).** We will administer the AUDIT to screen for potential alcohol use concerns. For individuals who score above the threshold on the AUDIT (≥ 8), we will administer the DIAMOND alcohol use disorder module to further evaluate participant eligibility.

Drug Use Disorder Identification Test (DUDIT; [80, 113]). We will administer the DUDIT to screen for potential drug use concerns. For individuals who score above the threshold on the DUDIT (≥ 6 for men; ≥ for women and nonbinary individuals), we will administer the DIAMOND substance use disorder module to further evaluate participant eligibility.

Insomnia Severity Index (ISI;[81, 83]). The ISI is a 7-item, well-validated index of nighttime and daytime insomnia symptoms**.**

Short Eating Disorder Examination Questionnaire (EDE-QS;[77]). The EDE-Q is a self-report measure designed to assess a broad range of eating-related symptoms, including restraint, eating concern, shape concern and weight concern [114]. We used the 12-item short form of the EDE-Q. This version has shown strong internal consistency (Cronbach’s α = 0.913, high temporal stability (ICC = 0.93), and scores are strongly correlated with the original EDE-Q scores (r’s > 0.81). It has also shown sensitivity in differentiating people with and without eating disorders.

Munich Chronotype Questionnaire (MCTQ; [84]). The MCTQ is designed to assess chronotype, with a focus on the midpoint of sleep during free days.

Brief Social Rhythms Scale (BSRS;[115]). The BSRS assesses the irregularity of engagement in daily activities such as mealtimes and social interaction on workdays and free days.

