### Potential mechanisms of change

To determine whether TRE specifically shifts sleep and day/night rhythms (hypothesized mechanisms), we will examine changes in sleep (the gold standard CORE CSD measures of quality of sleep and reduced variability in sleep midpoint, along with PROMIS sleep disturbance and sleep-related impairment) and day/night rhythms (BSRS and the MCTQ). To assess whether the sleep and light guidance offered as part of the TRE intervention leads to improved sleep hygiene, we will gather the Sleep Household Environment and In-Bed Behaviors [98].

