### Statistical analyses of secondary outcome measures

Intervention-related changes in secondary outcomes will be tested using repeated measures linear mixed model analyses to determine whether TRE leads to changes in sleep (core CSD, PROMIS Sleep Disturbance and Sleep-related Impairment), day/night rhythms (BSRS and the MCTQ), or emotion variability (as assessed using ecological momentary assessment) as compared to the Mediterranean Diet.

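### The BSRS total, used as evidence that TRE shifts day/night rhythms, includes mealtime regularity, which TRE partly assigns, so a TRE advantage could partly reflect adherence

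*Protocol article*

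**What the plan says.** All references are to the protocol article.

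- **Content of the scale** (Screening questionnaires): "The BSRS assesses the irregularity of engagement in daily activities such as mealtimes and social interaction on workdays and free days". The number of items, and how many concern meals, are not given.
- **TRE arm** (Time-Restricted eating): "TRE involves restricting the window of eating to 10 h per day", and participants are to "follow their habitual diet within the specified consistent 10-h period".
- **Comparator arm** (Mediterranean diet): the section sets food groups, servings and limits on some foods. To match burden, "participants in the Mediterranean diet condition will also be asked to log their food intake using the app". It describes no rule on when to eat.
- **Mechanism role** (Potential mechanisms of change): "To determine whether TRE specifically shifts sleep and day/night rhythms (hypothesized mechanisms), we will examine changes in sleep". The same sentence names the BSRS and the Munich Chronotype Questionnaire (MCTQ) as the day/night-rhythm measures.
- **Between-arm test** (Statistical analyses of secondary outcome measures): mixed models will test for changes in sleep, "day/night rhythms (BSRS and the MCTQ), or emotion variability (as assessed using ecological momentary assessment) as compared to the Mediterranean Diet".
- **Second role** (Secondary hypotheses): a brief social rhythm questionnaire, which I take to be the same instrument, is the measure for regularity of daily routines.
- **Adherence** (Food intake schedules): TRE adherence is scored from the times of the first and last caloric intake of the day.

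**The concern.** A mechanism measure should be able to stay still when the assigned behaviour is followed and nothing downstream changes. The BSRS total may not have that property in this trial. TRE asks for a consistent eating window; the BSRS rates, among other things, how irregular mealtimes are. A participant who keeps the window and changes nothing else could score as less irregular. Only one arm is given such an instruction, so the effect does not cancel in the comparison, and its direction favours TRE.

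What is at stake is one interpretive step. The rationale is that the timing of food acts on other diurnal rhythms. The informative finding would be a change in sleep, activity or social rhythms, beyond the change in eating times that the protocol already scores as adherence. A between-arm difference on the BSRS total cannot by itself tell these apart. Table 2 schedules the BSRS at mid-intervention, post-intervention and at 6, 9 and 15 months, so the ambiguity could recur for as long as participants keep to the plan.

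**Working it through.** **1. Is the overlap in the text?** Setting the sections side by side:

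| Question | Where | Answer |
|---|---|---|
| Does the BSRS include mealtime regularity? | Screening questionnaires | Yes, mealtimes are a named example |
| Does TRE assign it? | Time-Restricted eating | Partly: a consistent 10-h window bounds first and last intake; meals inside it are not fixed |
| Does the comparator assign it? | Mediterranean diet | No timing rule is described |
| Is intake timing already scored as adherence? | Food intake schedules | Yes |
| Is the BSRS tested between arms as a rhythm measure? | Potential mechanisms of change; Statistical analyses of secondary outcome measures | Yes |

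The overlap is real, partial and one-sided.

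**2. How large could it be?** The article gives no figure to reproduce, and none from which the size follows. The following is an illustration only.

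*Assumed:* m = 10 equally weighted items, each with SD 1; k = 1 to 3 mealtime items; a mean shift δ = 0.5 to 1.0 SD on those items in the TRE arm only; inter-item correlation r = 0.2 to 0.4; no change on any other item. *From the Statistical analysis plan section:* 200 analysed, hence 100 per arm at 1:1.

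The SD of the total is √(m + m(m−1)r), so the standardised difference on the total is

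d = kδ / √(m + m(m−1)r).

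The denominators are √28 = 5.29 (r = 0.2), √37 = 6.08 (r = 0.3) and √46 = 6.78 (r = 0.4). The chance of two-sided p < 0.05 comes from the noncentral t with 198 degrees of freedom and noncentrality d√50.

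| k | δ | r | d | Chance of p < 0.05 |
|---|---|---|---|---|
| 1 | 0.5 | 0.4 | 0.5/6.78 = 0.07 | 8% |
| 2 | 0.8 | 0.3 | 1.6/6.08 = 0.26 | 46% |
| 3 | 1.0 | 0.3 | 3.0/6.08 = 0.49 | 93% |
| 3 | 1.0 | 0.2 | 3.0/5.29 = 0.57 | 98% |

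The last column is power to detect a true difference in the total score, one that comes entirely from the mealtime items. It is not a type I error rate and should not be compared with 5%. The upper rows of the range also need a large average shift across the whole randomised arm, including people who do not adhere.

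**3. What would dropping the mealtime items cost in reliability?** With α = kr/(1 + (k−1)r), where k is now the number of items kept, and r = 0.3:

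- 10 items: 3.0/3.7 = 0.81
- 8 items: 2.4/3.1 = 0.77
- 7 items: 2.1/2.8 = 0.75

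**The case against.** The strongest reply is that mealtimes belong to what the BSRS measures. The Secondary hypotheses section uses it for regularity of daily routines, and the section on the applicability of TRE to mood disorders motivates the trial partly by irregular eating rhythms in remitted bipolar disorder. Under that hypothesis, more regular meals are a genuine gain. This stands, and it confines the point to the mechanism reading.

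Second, a reader might infer that the mealtime items are simply a compliance measure. The article does not support that. TRE compliance is keeping to a planned window; the BSRS rates irregularity. Someone with regular meals spread over a long day could comply fully and move little on the scale, and TRE sets no meal times inside the window.

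Third, a reader might infer that the mechanism claim rests on the BSRS, or that an adherence effect would necessarily be reported as mechanism. Neither follows. The sleep diary, the PROMIS sleep scales and the MCTQ are examined alongside it, and none is described as having meal content. If only mealtimes changed, the BSRS could move while the others did not. The Discussion also concedes that the trial was not designed to assess circadian processes closely.

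Fourth, item-level scoring of a secondary scale is commonly left to the SAP, which is not shown. Silence on scoring is therefore not the fault. What remains is that the article assigns a mechanism reading to a scale whose stated content overlaps the instruction given to one arm.

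**Conclusion.** The point holds in a limited form. The BSRS includes mealtime regularity, TRE partly assigns it through a consistent window, and the comparator does not. A TRE advantage on the total could therefore partly reflect adherence. The direction favours TRE. The size is unknown: 0.07 to 0.57 SD under assumed item counts, correlations and shifts, so it may be negligible or may be enough to decide the test. The article supports neither end of that range.

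The overlap bears on the statement that TRE "To determine whether TRE specifically shifts sleep and day/night rhythms (hypothesized mechanisms") and on the between-arm test that follows from it. It does not undermine the routines hypothesis, and it does not touch the MADRS, YMRS, LIFE or quality-of-life results. This is an inexpensive improvement to the interpretation of one secondary measure.

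**What to change.** Prespecify the following before the allocation is unblinded for analysis:

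1. Keep the full BSRS score for the hypothesis on regularity of daily routines. This also keeps it comparable with the screening threshold (a score of 30 or more, in Online screening) and with other studies.
2. For the mechanism claim, make the between-arm test on a BSRS score without the mealtime items.
3. Report the mealtime items by arm as a manipulation check, next to the adherence results from the food logs.
4. Claim a rhythm mechanism only if the non-meal BSRS score or the sleep-based measures support it.

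This takes a few sentences in the analysis plan. It needs no new data, provided that item responses are stored, and no change to either intervention. The downside is a shorter, non-standard score with somewhat lower reliability: about 0.75 to 0.77 against 0.81 under the assumptions above.
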